## Discussion

In this paper, we presented the rationale and design of a single-center, open, RCT. With this trial, we will evaluate the clinical effectiveness of a smart technology intervention in patients with STEMI and NST-ACS.

### Clinical Effectiveness

It is expected that with daily monitoring of ECG, BP, weight, and steps, data will allow for early detection of high BP and the development of arrhythmias. For this study, the percentage of patients with controlled BP at 12 months has been chosen as primary outcome. Controlled BP is associated with lower risks of death, recurrent PCI, and stroke in patients who suffered from ACS. Therefore, the European guidelines recommend tight BP control via medication and lifestyle advice.

Percentages of 1-year mortality after STEMI or NST-ACS vary, but have been reported to be under 10% [26]. With a sample size of 200, it is expected that this study is underpowered to detect a significant difference in mortality between the intervention group and control group. It is emphasized that it is not the primary objective of this study to demonstrate a difference in mortality. This study is intended to investigate whether regular monitoring of clinical parameters (including BP) can lead to better control of those parameters, therefore improving surrogate outcomes in these patients.

### Patient Compliance

All devices used in the intervention group are designed for the consumer market. Patients will receive assistance with installation of the devices. After measurements, data will automatically be transferred to the hospital. It is expected that this automation will help to facilitate accurate and timely transmission, which might enhance patient compliance. To test this hypothesis, all reminders sent to patients for not having measured their data will be monitored. “No-shows” at digital outpatient clinic visits, and at the physical outpatient clinic visits, will be monitored as well. It is hypothesized that there will be no significant difference in the percentage of “no-shows” between the digital outpatient clinic visits and the physical outpatient clinic visits.

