### The Box

When randomized to *The Box* (Figure 2), patients will receive a box containing a weight scale, BP monitor, activity tracker, and a wearable ECG device. Patients will receive *The Box* before discharge and will be given the same written and oral information on the importance of medication adherence and lifestyle advices as the control group, in accordance with the European Guidelines on cardiovascular disease prevention in clinical practice [17]. The necessary apps will be downloaded on the patient’s smartphone; necessary accounts will be created and the installation of the devices will be carried out by a health care professional dedicated to the project. Afterwards, patients will be given oral instructions on the usage of the devices: they will be instructed to measure BP in a sitting position after five minutes of resting. The device should be applied to the left upper arm. Patients will be instructed to rest their left forearm on a table. Furthermore, a manual explaining the usage of the wearables (described below) will be handed over with *The Box*. Instruction videos are also available on YouTube. Patients who do not own a smartphone or tablet with iOS or Android OS but are willing to participate and be randomized to *The Box* will receive a smartphone. Patients will be instructed to use their own wireless Internet access (eg, home WiFi network). No mobile data network plan will be provided with the smartphone.

Patients will be instructed to record a single lead ECG, measure BP, and record their weight daily, preferably at the same time of day. Furthermore, participants will be asked to record a single lead ECG if any symptoms of possible cardiac origin occur (as interpreted by the patient). Lastly, patients will be instructed to wear their activity tracker during the day to track their daily number of steps, and at night to track the duration and quality of sleep. Patients will be told that measurements will be checked on a daily basis and that they will be contacted in cases of predefined data irregularities. Patients will be explicitly told that they cannot rely on the devices of *The Box* in emergency situations.

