### Nonadherence

If a patient does not send measurements from any of their four devices for 21 consecutive days, they will be considered nonadherent. A standardized email will be sent to the patient, stating that measurements have not been received and that they are urged to contact the hospital in case of any technical difficulties. If no answer is received within 21 days or no measurements are seen within 21 days, the patient will be called by telephone. Any technical difficulties or objections by the patient will be assessed and solved if possible. After this phone call, if the patient starts sending measurements, they will be considered adherent again. This patient will be sent a standardized email in case they become nonadherent again. If the patient does not start sending measurements, they will not be approached again by email or by telephone to try to affect their nonadherence. However, this patient will not be excluded from the trial, and will still be followed-up according to *The Box* protocol. If patients notify the hospital that they want to have regular outpatient clinic visits, they will be followed-up according to the regular follow-up protocol.

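### Counting reminders cannot test whether automatic data transfer enhances compliance, and the count does not track how often The Box patients measured

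*Protocol article*

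**What the plan says.** In the Discussion, under Patient Compliance, the protocol article sets out an expectation about automatic transfer: "It is expected that this automation will help to facilitate accurate and timely transmission, which might enhance patient compliance". The measure follows directly: "To test this hypothesis, all reminders sent to patients for not having measured their data will be monitored". No-shows at digital and physical visits are monitored too, but they record attendance, not measuring.

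The instruction against which compliance would be judged is in Methods, The Box: "Patients will be instructed to record a single lead ECG, measure BP, and record their weight daily, preferably at the same time of day".

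The reminder rule is in Methods, Nonadherence. The trigger is: "If a patient does not send measurements from any of their four devices for 21 consecutive days, they will be considered nonadherent". A standard email is sent, and then: "If no answer is received within 21 days or no measurements are seen within 21 days, the patient will be called by telephone". The rule has two endings. For a patient who resumes: "After this phone call, if the patient starts sending measurements, they will be considered adherent again", with a further email at a new lapse. For one who does not: "If the patient does not start sending measurements, they will not be approached again by email or by telephone to try to affect their nonadherence".

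A second contact route stands elsewhere in Methods. Textbox 2 (Data Integration in Electronic Medical Records) lists more than 7 consecutive days without data as a warning, separately for the BP monitor, the weight scale and the activity tracker. It lists no such warning for the ECG device. Reasons to Contact Patients says that listed irregularities lead to an email or call within 48 hours. The article does not say whether these contacts count as reminders, or how they fit with the 21-day rule and its stop clause.

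**The concern.** Two separate things are wrong with the stated measure.

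First, the hypothesis is comparative: automation enhances compliance relative to having no automation. The design contains no such comparison. Controls receive regular care without devices, and every patient in The Box group has automatic transfer.

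Second, contacts are generated by a rule that stops for patients who never resume and starts again for those who do. It also reacts only to unbroken silence of a set length, not to the share of days measured. A count of contacts therefore need not rise as use falls.

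What is at stake is the description of how much monitoring took place. Under Clinical Effectiveness the article says that the trial asks whether regular monitoring leads to better control. A reader of the BP result will want to know how regular the monitoring was, and reminders are the only measure of device use that the article names for compliance.

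**Working it through.** The article gives no figure for reminders or compliance, so there is nothing to reproduce. The check is to apply the rules as written to a few patterns of use.

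**Inputs from the article.** Follow-up of one year (365 days used). Measurement asked for daily. Email after 21 silent days, call after a further 21, then no more unless the patient resumes. Separate warning after more than 7 silent days.

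**Assumptions.** The patterns of use are illustrative. The 21-day trigger is read as silence on all four devices. Each 7-day gap is taken to prompt one contact per device, and the last column counts one device.

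**Step 1: is there a comparator?** Devices, reminders and automatic transfer all belong to The Box group only. The number of groups with devices but without automatic transfer is zero, so no value of the count can bear on the hypothesis.

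**Step 2: the cap.** A patient who never resumes is emailed at day 21 of silence and called at day 42, then left alone: 1 + 1 = 2 contacts, whether the last reading was on day 0 or day 30.

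**Step 3: patients who return.** Take a patient who is silent for 42 days (email, then call), resumes, and later is silent for 21 days (email). Contacts: 1 + 1 + 1 = 3. Days measured: 365 − 42 − 21 = 302, and 302/365 = 82.7%. This follows the article's wording exactly, since the repeat email is stated for a patient who resumes after the call. Three separate 21-day lapses ended after the email alone also give 365 − 3 × 21 = 302 days and 3 emails, but there the repeat email is inferred.

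**Step 4: sparse use.** Every 20 days: 365/20, or 18 readings, 18/365 = 4.9%. Weekly: 365/7, or 52 readings, 52/365 = 14.2%. Every 8 days: 45 readings, 45/365 = 12.3%, with exactly 7 silent days between readings, which is not more than 7. Every 9 days: 40 readings, 40/365 = 11.0%, with 8 silent days each time.

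| Pattern | Days measured | 21-day rule: contacts | 7-day warning: episodes |
|---|---|---|---|
| Daily | 100% | 0 | 0 |
| One 42-day and one 21-day lapse | 82.7% | 3 | 2 |
| Weekly | 14.2% | 0 | 0 |
| Every 8 days | 12.3% | 0 | 0 |
| Every 9 days | 11.0% | 0 | 40 |
| Stops at day 30 | 8.2% | 2 | 1 |
| Every 20 days | 4.9% | 0 | 18 |
| Never measures | 0% | 2 | 1 |

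Neither contact column orders the patients by use. The share of days does so by construction.

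**Step 5: permanent silence under the 7-day warning.** With one contact per gap the patient who never measures counts once. If the warning instead prompted contact on every flagged day, the count could reach 365 − 7 = 358, which would collide with the stop clause in Nonadherence. The article does not say which applies.

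**The case against.** The strongest reply is that this is one sentence in the Discussion of a journal article. Compliance is not among the outcomes under Study Outcomes and has no analysis under Statistical Analyses. The text says only that reminders will be monitored; it specifies no score or ranking. The stored data leave a fuller analysis open. All of that is true, and it limits the weight of the point. It does not remove it, because the sentence names a measure and says that it serves to test a hypothesis.

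Three stronger readings are tempting, and the article does not support them.

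- *A dropout can look better than an adherent patient.* A patient who measures daily has no reminders, and a dropout who triggers the rule has at least one. The inversion concerns patients who lapse and resume, each of whom did meet the article's own definition of nonadherent for a time.
- *Sparse use goes unseen altogether.* The 7-day warnings would plausibly count as reminders, since the sentence speaks of all of them. They would then catch use every 20 days (18 episodes), and their BP and weight entries would catch a patient who only wears the tracker. What remains unseen is roughly weekly use.
- *Few reminders could conceal mass early dropout.* With 200 patients randomised 1:1, The Box group has about 100. If 50 stopped for good early on, the 21-day rule alone would give 50 × 2 = 100 contacts, against none if all measured daily. The total would rise. It could not be decoded, however: 33 patients with three contacts each and 82.7% of days measured give 33 × 3 = 99.

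Nor does the article say that reminders will be used to explain a null BP result.

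**Conclusion.** The point holds. The reminder count cannot test the automation hypothesis, because there is no comparator; this does not depend on how reminders are counted. As a measure of device compliance the count is poor. It is capped at two contacts for a patient who never resumes, against three for one who measured on 82.7% of days, and it cannot tell weekly use (14.2% of days) from daily use even when the 7-day warnings are included.

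The figures rest on illustrative patterns over 365 days, on reading the 21-day trigger as silence on all four devices, and on one contact per 7-day gap. The cap and the failure to see weekly use follow from the rules themselves.

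The intention-to-treat comparison of BP control at 12 months is untouched. This is a worthwhile correction to a stated secondary description, not a threat to the trial's main conclusion.

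**What to change.** In Patient Compliance:

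- Describe compliance in all patients randomised to The Box as the proportion of follow-up days with a transmitted measurement, separately for BP, ECG, weight and activity tracker, and by period (for example months 0–3, 3–6 and 6–12). Add the time to last BP transmission.
- Keep the number of reminders as a measure of staff workload, and state which contacts it includes.
- Reword the automation hypothesis as a description of compliance under automatic transfer, since nothing in the design tests its effect.

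In Methods, the investigators need to reconcile the 7-day contact passages (Textbox 2 and Reasons to Contact Patients) with the 21-day rule and stop clause in Nonadherence. Which contact rule should apply is for them to decide.

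The cost is a wording change and a short descriptive analysis. BP, weight and activity data are already imported into the electronic medical record, and the ECGs are held in the manufacturer's cloud, where linked physician accounts can view them. No new data collection is needed.

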**Methods:**

In this single center, open, randomized controlled trial patients who suffered from STEMI or NST-ACS will be randomized 1:1 to an intervention group or control group. Both groups will be followed up to one year after the index event. The intervention group will take daily measurements with a smartphone-compatible electrocardiogram device, blood pressure (BP) monitor, weight scale, and activity tracker. Furthermore, two of four outpatient clinic visits will be replaced by electronic visits (1 and 6 months after index event). The control group will receive regular care, consisting of four outpatient clinic visits (1, 3, 6, and 12 months after index event). All patients will be asked to fill in validated questionnaires about patient satisfaction, quality of life, propensity of medication adherence, and physical activity.

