## Methods

### Study Design (Design, Randomization, and Follow-Up)

*The Box* is a single-center open RCT, and is a parallel group study. The study will be conducted at the Leiden University Medical Center (LUMC), a tertiary care hospital in Leiden, The Netherlands. The trial is registered under clinical trial number NCT02976376 (Clinicaltrials.gov) and NL56453.058.16 (Toetsingonline.nl). After inclusion, patients will be randomized 1:1 to either *The Box* (intervention group) or to regular follow-up (control group). Block randomization per 10 participants will be performed. Randomization will be stratified per primary diagnosis (STEMI or NST-ACS) and per age (<50, 51-60, 61-70, 71-80, and >80 years). A website will be used to generate randomization lists [16].

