In addition to daily measurements, the first and third of the four standard outpatient clinic visits will be replaced by an electronic visit, in which the patient will communicate with the doctor or nurse practitioner via a secured video connection. The content of the interview will be comparable to the content of a regular outpatient clinic visit. The same doctors and nurse practitioners will perform the regular outpatient clinic visits and the digital outpatient clinic visits. In the intervention group, the 10-second 12-lead ECG and the laboratory testing one month after the index event will not be performed. Moreover, the 10-second 12-lead ECG, the 24-hour Holter ECG, laboratory testing, and the TTE 6 months after the index event will not be performed (Figure 1).

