### Statistical Analyses

A power calculation was done using R software [24], which is based on a comparison of two proportions of patients with controlled BP (defined as an SBP of 139 mmHg or less and a DBP of 89 mmHg or less). We hypothesize that in the *The Box* group, 95% of the patients will achieve controlled BP, while in the control group, 75% will achieve controlled BP [25]. For this calculation, an alpha of 0.05, a beta of 0.20, and a margin of 0.07 were chosen, yielding a sample size of 200 patients.

Data will be analyzed according to the intention-to-treat principle. Causes of missing data will be tabulated (Multimedia Appendix 1). The percentage of missing data is expected to be low. Therefore, complete case analyses will be done. Analyses will be based on the missing-at-random assumption. If the percentage of missing values exceeds 7%, multiple imputation will be applied in the analysis of the data.

After finishing the study (defined as the last patient’s last visit), the proportion of patients with controlled BP will be compared with a Chi-square test. Logistic regression might be done if serious imbalances of baseline variables exist, to correct for potential confounding variables. Percentages of patients with controlled BP at three months (secondary outcome 1), and percentages of patients in which a previously unknown sustained arrhythmia is detected, will also be compared with a Chi-square test.

Scores of questionnaires (patient satisfaction questionnaire, MMAS-8 scale, iPAQ questionnaire, and SF-36 questionnaire) and health care utilization will be compared using an independent t-test. Major Adverse Cardiac Events (MACEs) will only be reported. As the study is underpowered, no statistics will be done on MACEs. The numbers will be hypothesis-generating.

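### The expected no-show comparison sets digital against physical visits, which mixes visit mode with month and pools both arms, and a non-significant result without a margin would not show similar attendance

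*Protocol article*

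**What the plan says.** In the Discussion of the protocol article, under Patient Compliance, missed digital and physical visits are to be monitored. The expectation follows: "It is hypothesized that there will be no significant difference in the percentage of" missed visits. The contrast is drawn by visit type, "between the digital outpatient clinic visits and the physical outpatient clinic visits". The sentence gives no margin, no expected rate and no interval.

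The Box section says that "the first and third of the four standard outpatient clinic visits will be replaced by an electronic visit". Regular Follow-Up places the four standard visits at about 1, 3, 6 and 12 months, and the abstract gives the electronic visits as months 1 and 6. The control arm attends the clinic at all four.

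Under Nonadherence: "If patients notify the hospital that they want to have regular outpatient clinic visits, they will be followed-up according to the regular follow-up protocol".

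Statistical Analyses states the intention-to-treat principle. Its power calculation concerns blood pressure only. No-shows are not among the primary or secondary outcomes in Study Outcomes and have no assigned test.

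**The concern.** Replacing two of the four clinic visits is a defining part of the intervention, and no-shows are the attendance evidence that the article offers for it. Three features weaken that evidence.

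- **Mode is tied to month.** Digital visits occur at months 1 and 6 only, whereas physical visits cover all four time points. Any change in attendance over the year can appear as an effect of visit mode.
- **The randomised comparison is lost.** The physical group contains every control visit and half of The Box visits. If visits are classified by the type received, Box patients who ask for clinic visits move from the digital to the physical group. The digital figure then rests on those content with video visits.
- **The expectation is the absence of significance.** Without a margin, a non-significant test leaves open how large a difference remains plausible.

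**Working it through.** **Inputs.** From the article: 200 patients randomised 1:1, so about 100 per arm; digital visits at months 1 and 6 in The Box arm; clinic visits at months 1, 3, 6 and 12 in the control arm and at months 3 and 12 in The Box arm. The article gives no rate, power or margin for no-shows, so there is no figure of its own to reproduce. The margin of 0.07 belongs to the blood pressure calculation. Assumed here: the no-show rates, shown as ranges; a two-sided alpha of 0.05, since sidedness is not stated; no attrition.

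**Visit counts.** Digital: 100 × 2 = 200. Physical: 100 × 4 + 100 × 2 = 600.

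**Drift with no true mode effect.** Let r1, r3, r6 and r12 be the no-show rates by month, equal in both arms and both modes.

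Digital = (r1 + r6)/2. Physical = [(r1 + r3 + r6 + r12) + (r3 + r12)]/6.

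| Assumed rates, months 1/3/6/12 | Digital | Physical | Spurious difference |
|---|---|---|---|
| 2/4/6/10% | (2 + 6)/2 = 4.0% | (22 + 14)/6 = 6.0% | −2.0 points |
| 4/6/8/12% | (4 + 8)/2 = 6.0% | (30 + 18)/6 = 8.0% | −2.0 points |
| 10/8/6/4% | (10 + 6)/2 = 8.0% | (28 + 12)/6 = 6.7% | +1.3 points |

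**Power to detect a doubling.** Power = Φ{[|p1 − p2| − 1.96·√(p̄(1 − p̄)(1/n1 + 1/n2))] / √(p1(1 − p1)/n1 + p2(1 − p2)/n2)}, where p̄ is the pooled rate and visits are treated as independent.

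Worked case, 5% of 600 physical against 10% of 200 digital visits: p̄ = (30 + 20)/800 = 0.0625. The pooled standard error is 0.01976 and the unpooled one 0.02300. Then (0.05 − 1.96 × 0.01976)/0.02300 = 0.49, so power is about 69%.

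| Doubling | As stated, 200 v 600 | By arm, months 1 and 6, 200 v 200 |
|---|---|---|
| 3% to 6% | 49% | 30% |
| 5% to 10% | 69% | 48% |
| 8% to 16% | 87% | 69% |
| 10% to 20% | 94% | 80% |

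On the stated contrast, a doubling is more likely missed than found only when the base rate is below about 3.1%, and power reaches 80% at about 6.6%. For 200 v 200 the corresponding base rates are about 5.3% and 10.0%. Exact enumeration of the chi-square test agrees closely (69% and 47% for 5% to 10%).

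**Drift and a true doubling together, stated contrast.** With 4/6/8/12% and the digital rate doubled, the comparison is 12% v 8% and power is 41%. With 10/8/6/4% it is 16% v 6.7% and power is 96%. The same relative effect can be hidden or magnified by timing alone.

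**Switching.** Moving 5, 10 or 20 Box patients to clinic visits changes the counts to 190 v 610, 180 v 620 or 160 v 640. Power for 5% v 10% falls from 69% to 68%, 66% or 64%. The selection effect of who switches cannot be computed from the article.

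**Precision of the by-arm comparison.** At 5% in both arms the 95% CI half-width is 1.96 × √(2 × 0.05 × 0.95/200) = 4.3 points; at 10% it is 5.9 points. Both ignore within-patient correlation. In a simulation with a correlation of 0.2, a test treating visits as independent rejected about 7% of the time when the arms did not differ, so the two visits per patient need to be allowed for.

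**The case against.** The strongest reply is that this is one sentence of expectation in a Discussion, about an item that is monitored and is neither a listed outcome nor assigned a test. That is correct, and it sets the weight of the point. A condensed article may also leave denominators and clustering to the full protocol. That is fair too, and their absence is not held against it. The contrast and the hypothesis, however, are stated, and it is those that are poorly chosen.

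Four stronger readings are tempting, and the article supports none of them.

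- **A doubling of missed visits would probably go undetected.** This needs a no-show rate that the article does not give. On the stated contrast, a doubling from 5% has about 69% power. The 48% figure belongs to the by-arm comparison recommended below.
- **Digital visits will look better because they come earlier.** The sign depends on the drift: falling rates reverse the bias.
- **Switchers will be analysed as treated.** The Nonadherence section describes follow-up, not analysis, and Statistical Analyses states intention to treat. Switchers could change group if the visit-type wording is followed literally, but no text says that they will.
- **The trial will claim equivalence.** The article makes no such claim for no-shows. The issue is only that non-significance could not support one.

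**Conclusion.** The point holds as a minor one. Taken at its words, the contrast confounds visit mode with month, pools randomised arms and leaves room for switchers to change group. Under the illustrative drifts the spurious difference ranges from −2.0 to +1.3 points; the true size and direction are unknown because the article gives no rates. A non-significant result without a margin would not show similar attendance at any level of power. How likely a doubling is to be missed varies widely with the base rate: power runs from 49% at 3% to 87% at 8% on the stated contrast. These figures assume about 100 patients per arm, a two-sided 5% test and independent visits. The primary and listed secondary outcomes are not affected.

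**What to change.** Compare no-shows by randomised arm at months 1 and 6, the two visits at which the arms differ. Count Box patients who moved to clinic visits in The Box arm, in line with the intention-to-treat principle in Statistical Analyses. Report the difference with a 95% CI that allows for two visits per patient. Replace the expectation of no significant difference with the estimate and its interval, and do not infer equal attendance from a non-significant result.

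The change is one of wording, since attendance is already to be monitored. The price is precision: 200 v 200 visits replace 200 v 600, so power for 5% v 10% falls from about 69% to about 48%, and the CI half-width at a 5% rate is about 4.3 points before allowing for within-patient correlation. In return, the timing bias goes and the randomised comparison is kept.
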